#### 2.9.2. Blinding

There will be a separation between the assignment generator and those carrying out the assignment. Implementation of the intervention will be performed by personnel not involved in the data collection. Clinicians, clinical research associates, and statisticians will be blinded regarding the group category at the time of the evaluation and analysis. Identification codes will be retained by the study monitor and will not be opened until the end of the study.

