#### 2.6.3. Follow-Up Visits

Visits will be made according to the pregnant woman’s monthly follow-up schedule (Table 1). Obstetric clinical examination, biological analysis, and oral clinical examination will performed at each visit. Interdental sampling will be realized for all participants at 6 and 8 months of gestation. 

Participants in the intervention group will be asked about compliance with the study treatment (control of hygiene methods and techniques, and acceptance).

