### 2.9. Assignment of Interventions

#### 2.9.1. Allocation

In this conventional (parallel) cluster randomized trial, antenatal care clinics will be randomized to either the intervention or control arm at the start of the trial and remain in that arm for the duration of the study [35]. The allocation schedule for randomly assigning clinics will be computer generated, and stratified by study site and clinic characteristics at a central location (UR4129 Research Unit, University Lyon, France) by the study officer of the research using e-CRF Voozalyon 1.3 (Voozanoo, Caluire, France). Once the local investigators are operational for the implementation of the training seminars for the clinic staff, the treatment allocation will be sent by email by the study officer to the principal investigator of the selected site. Eligible adults per site will be included in the study in the order of inclusion until the number of subjects per site specified in the protocol is reached.

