### 2.10. Data Collection, Management, Analysis

#### 2.10.1. Data Collection Methods

Using e-CRF in each site, a unique identification code will be assigned to each subject. All documents, forms, and data files will be labeled with this identification code. Each subject will be counted in the screening and enrollment record. Data from study participants will be collected in the form of anonymized case report forms. The investigator will complete the e-CRF. The investigator can enter and save the collected data in the study computer. The monitor will be informed that the CRF has been fully completed and that no changes have been made. The data can be verified by the monitor and used for internal evaluations. The central study officer will have permanent access via the e-CRF, throughout the study, to the study computers of the 16 different study sites.

The data collected and the questionnaires will be archived for at least 10 years, personal data such as names, addresses, and birthdays will not be kept.

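### The claim that clinicians are blinded cannot hold for site investigators and cannot be assured for clinic clinicians, because each clinic sits wholly in one arm and its lead investigator is told which

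*Protocol article*

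**What the plan says.** Section 2.9.2 (Blinding) makes the claim without exception: "Clinicians, clinical research associates, and statisticians will be blinded regarding the group category at the time of the evaluation and analysis". It adds two supports. The staff who deliver the intervention do not collect data, and "Identification codes will be retained by the study monitor and will not be opened until the end of the study".

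Section 2.9.1 (Allocation) says that "antenatal care clinics will be randomized to either the intervention or control arm at the start of the trial and remain in that arm". The arm is disclosed when the site is ready to run its staff seminars, and the recipient is named: "the treatment allocation will be sent by email by the study officer to the principal investigator of the selected site".

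Other sections bear on who could know the arm and who produces the primary outcome:

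- Section 2.10.1 (Data Collection Methods): "The investigator will complete the e-CRF".
- Section 2.6.3 (Follow-Up Visits): "Participants in the intervention group will be asked about compliance with the study treatment". No matching questions are listed for controls.
- Section 2.6.4 (Delivery Data Collection): occurrence of PE is taken from medical records after delivery.
- Section 2.5.1 (Primary Outcome Measures): PE is defined by blood pressure thresholds, met on readings 4 h apart or by one more extreme reading, together with proteinuria.
- Section 2.6.2: the periodontists have their own blinding statement, but they assess secondary outcomes.

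**The concern.** In an individually randomised trial, sealed codes can hide a woman's group from the staff who see her. Here every woman at a clinic has the same group, so anyone who knows the clinic's arm knows hers. At least one person at each site is told that arm by design. The document describes nothing that would keep it from the staff who measure blood pressure and record PE.

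This reaches the primary outcome. Taking a pressure, deciding to repeat it and entering a diagnosis in the record are all done locally. If vigilance or recording differs by arm, the difference enters the PE comparison directly. The published report would also claim blinded clinician assessment that the design does not support.

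**Working it through.** **Setting the sections side by side**

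1. *Who is said to be blinded.* Section 2.9.2 names clinicians, clinical research associates and statisticians, at evaluation and analysis.
2. *Who is told the arm.* Section 2.9.1 names the site principal investigator, who receives it by email before recruitment is under way at the site.
3. *What that reveals.* With one fixed arm per clinic, the clinic's arm identifies the arm of all 55 women recruited there (section 2.8).
4. *Who enters the data.* Section 2.10.1 names the investigator. It does not say whether this is always the person who received the email, but no second, masked investigator is described.
5. *Where PE comes from.* Section 2.6.4 names medical records, which are kept by local staff. No masked or central classification is described.
6. *What the supports achieve.* Separating delivery staff from data collectors is a real but partial step, because it does not hide a clinic-wide allocation. Holding individual codes does not hide the arm within a single-arm clinic, although it may still support masked central analysis.

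**Illustration of size**

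The plan states no figure for this, so there is none to reproduce. Design inputs from sections 2.7 and 2.8: control PE rate 20%, intracluster correlation 0.03, one-sided 5% test, 440 women per arm, 55 per clinic, 16 clinics. Assumptions not in the documents: no true effect (20% in both arms), and a chosen fraction of PE cases unrecorded in the intervention arm only.

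- Design effect = 1 + (55 − 1) × 0.03 = 2.62.
- Effective size per arm = 440 / 2.62 = 167.9.
- SE = √{[p₁(1 − p₁) + p₂(1 − p₂)] / 167.9}.
- Chance of a significant benefit = Φ[(p₁ − p₂)/SE − 1.645].

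| Under-recording | Apparent rates | SE | Difference / SE | Chance of false benefit (normal) |
|---|---|---|---|---|
| 5% | 20% vs 19% | 0.0432 | 0.231 | 0.079 |
| 10% | 20% vs 18% | 0.0428 | 0.467 | 0.119 |
| 20% | 20% vs 16% | 0.0419 | 0.955 | 0.245 |

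With a t reference on 14 degrees of freedom (16 clinics − 2), the 10% and 20% rows become 0.115 and 0.231.

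The direction is also assumed. If intervention clinics instead recorded 10% more cases (20% vs 22%), SE = √[(0.16 + 0.1716)/167.9] = 0.0444 and the chance is Φ(−0.450 − 1.645), about 0.02. The bias would then work against the intervention.

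**The case against.** Lack of blinding at clinic level is inherent in a behavioural cluster trial, and an article may leave to the full protocol who measures, who asks and who classifies. Blood pressure and proteinuria are scheduled at every visit for all women (Table 1), and the PE definition uses numeric thresholds, some met by a single reading. That narrows the room for discretion. These points stand, but they do not rescue section 2.9.2. It is an affirmative statement that other sections of the same document undercut, not a missing detail.

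A reader might infer more, and the documents do not support it:

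- *That no blinding exists at all.* Nothing refutes blinding of the central statisticians, and nothing shows that clinical research associates are told the arm.
- *That the seminars unblind clinic staff.* Their content, and whether both arms attend, is not stated.
- *That the compliance questions unblind the examiners.* Section 2.6.3 does not say who asks them or when. The delivery staff could do so after the examination.
- *That the periodontists know the arm.* Section 2.6.2 says they are blinded and places two at each site. It does not say they belong to the clinic or receive the allocation.
- *That the sealed codes are useless.* They may serve masked analysis.
- *That the false-positive rate will be 12% or 25%.* Both the size and the direction of under-recording are assumed.

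**Conclusion.** The concern holds in a limited form. As written, clinician blinding contradicts the allocation procedure: it cannot hold for a site investigator who is told the arm, and it cannot be assured for other clinicians in a single-arm clinic. That every clinician would in fact know the arm is a strong inference, not a stated fact. Blinding of the central statisticians, and possibly of the periodontists, survives.

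The effect on the primary result cannot be sized from the documents. The calculations show only that modest under-recording in one arm would matter: about 12% false positives at 10% under-recording and about 23–25% at 20%, against a nominal 5%. These figures rest on no true effect, the plan's own 0.03 correlation and cluster size, and an assumed degree and direction of under-recording.

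**What to change.** 1. Rewrite section 2.9.2 to say that participants, site investigators and clinic clinicians are not blinded. Limit the claim to the central statisticians, working with coded arms, and to any examiners who can in fact be kept unaware of the clinic's arm. For the periodontists, say how this is achieved or drop the claim.
2. Keep the sentence on identification codes only as a safeguard for masked central analysis.
3. Classify PE centrally against the section 2.5.1 definition, with arm and clinic masked. Use dated blood pressure and proteinuria values from the scheduled visits and from the medical and delivery records. Scheduled e-CRF values alone could miss PE arising between visits or around delivery, and the article does not say that the e-CRF holds the repeat readings 4 h apart.
4. State that the implementing staff ask the compliance questions, after the examination, and keep those answers out of the file used for masked classification, since only one arm has them.
5. Report arm-dependent measurement as a remaining possible bias. Central classification reduces bias in labelling a case, but it cannot restore a reading that was never taken or repeated.

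The cost is a less favourable blinding claim, some extra data extraction from records and a classification program. Randomisation and sample size are unaffected by this change.

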### 2.10. Data Collection, Management, Analysis

#### 2.10.1. Data Collection Methods

Using e-CRF in each site, a unique identification code will be assigned to each subject. All documents, forms, and data files will be labeled with this identification code. Each subject will be counted in the screening and enrollment record. Data from study participants will be collected in the form of anonymized case report forms. The investigator will complete the e-CRF. The investigator can enter and save the collected data in the study computer. The monitor will be informed that the CRF has been fully completed and that no changes have been made. The data can be verified by the monitor and used for internal evaluations. The central study officer will have permanent access via the e-CRF, throughout the study, to the study computers of the 16 different study sites.

The data collected and the questionnaires will be archived for at least 10 years, personal data such as names, addresses, and birthdays will not be kept.

#### 2.10.2. Data Management

Personal and experimental data will be analyzed without any personal characteristics using a unique identification code. Subjects can be traced through the subject re-identification record, which will be kept only at the clinical investigation site. Signed informed consent forms will be retained only at the clinical investigation site.

#### 2.10.3. Statistical Methods

The final analysis of the data will be based on intention-to-treat and will be performed with the STATA MP 16.0 software (College Station, TX 77845, USA). All principal statistical analyses will be based on the clusters as allocated in the randomization [36]. Intention-to-treat analyses will be performed on the imputed data from all patients using multiple imputation by chained equations, based on a Monte Carlo–Markov chain algorithm under missing at random data hypothesis. Unilateral analysis to study the superiority of intervention over control group will be programmed. Data entry and preliminary checks for error and internal validity will be carried out at each study site, with corresponding statistical analyses conducted at a central level. A series of explanatory analyses will also be conducted in which clinics and/or individuals deviating from the protocol will be excluded. Additionally, per-protocol analysis using the same methodology as the intention-to-treat analyses will be performed based on participants with a complete set of outcome data at endpoint.

The main analytical technique used to assess the effect of intervention on the primary outcome will be an application of the Mantel–Haenszel test adapted to the cluster randomization design. Baseline tables will be created comparing the intervention groups with respect to both cluster-level and individual-level risk factors. 

Groups will be compared as at randomization. The primary endpoint will be estimated by the Kaplan–Meier method (survival analysis) and comparison of the different groups by the Log Rank test (*p* < 0.05). A multivariate analysis by a Cox regression model will be used to explore the relationship between the risk function associated with PE and the intervention after adjustment for site, amenorrhea at inclusion, gestational age, maternal age, and periodontal parameters at inclusion. Continuous outcome variables will be analyzed using mixed model regression, with the clinic status treated as a random effect. Analyses will also be conducted to explore the possibility of an interaction effect between intervention and clinic size. All statistical analyses performed will account for the within-clinic correlation that would invalidate the application of standard statistical methods. The results will be communicated according to CONSORT guidelines.

Secondary analyses will also be performed comparing, as at randomization, the: (i) evolution of the pathogenic bacterial load of the interdental microbiota in the pregnant women intervention group compared to the control group, (ii) evolution of clinical signs of periodontal conditions in the pregnant women intervention group compared to the control group, and (iii) effect of individual oral prophylaxis during pregnancy on the risk of adverse perinatal outcomes. For dental clinical outcomes, mean and median values of clinical parameters for all oral, lingual/palatal, and proximal sites will be calculated per patient. Variations between the first and follow-up visits will be calculated.

Microbiological variables will be presented as total anaerobic counts, frequency of detection of target pathogens, counts of each pathogen studied, and proportions of each pathogen in the total microbiota. Total anaerobic counts will be log-transformed to match a normal distribution. 

The Shapiro–Wilk goodness-of-fit test and box plots will be used to determine the normal distribution of quantitative variables. Differences between groups at baseline and at follow-up visits will be determined by paired t-test or Mann–Whitney U tests for quantitative outcomes. In addition, clinical variables will be compared to repeated measures by ANOVA with Bonferroni post hoc correction controlling for visit for within-group comparisons, group (intervention or control) for between-group comparisons, and interaction between amenorrhea time and group. 

Results will be considered statistically significant at *p* < 0.05.

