### 2.5. Outcomes

#### 2.5.1. Primary Outcome Measures

Primary outcome measure will be the incidence of PE from baseline during the pregnancy. PE is defined as diastolic pressure >90 mm Hg after two 4 h intervals or >110 mm Hg once; systolic pressure >140 mm Hg after two 4 h intervals or >160 mm Hg once, after 20 weeks of gestation in combination with proteinuria 2+ or more; >300 mg/24 h, >500 mg/L, or urinary protein/creatinine ratio >0.034 g/mmol.

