### 2.7. Sample Size

Reduction in PE will be considered the primary outcome variable, and an estimate of the mean difference in PE reduction will be used to calculate the sample size. The primary acceptance criterion will be the PE effect of the evaluated medical devices showing at least a moderate effect of 20%.

To show a reduction in PE from 20% to 12% (with alpha = 5%, beta = 80%), coefficient of intraclass correlation of 0.03 and in a unilateral proportion test, we initially calculated 440 subjects per group. Assuming a potential dropout rate of 10%, 880 participants were determined as the target for patient inclusion.

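### The analysis labelled per-protocol is defined only by complete outcome data, so it is a complete-case analysis under the wrong name

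*Protocol article*

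**What the plan says.** Section 2.10.3 of the protocol article plans three analyses that differ in who is included.

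- The main one is by intention to treat: "Intention-to-treat analyses will be performed on the imputed data from all patients using multiple imputation by chained equations", under a missing-at-random assumption.
- The second is an explanatory series in which "clinics and/or individuals deviating from the protocol will be excluded".
- The third is introduced as an addition: a "per-protocol analysis using the same methodology as the intention-to-treat analyses", which "will be performed based on participants with a complete set of outcome data at endpoint".

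On adherence data, section 2.6.3 says: "Participants in the intervention group will be asked about compliance with the study treatment". No matching question is described for the control group.

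On outcomes, section 2.5.1 states: "Primary outcome measure will be the incidence of PE from baseline during the pregnancy". Section 2.5.2 adds change in bacterial load, periodontal scores, low birth weight and preterm delivery. Under section 2.6.4, occurrence of PE, length of gestation and birth weight are taken from medical records after delivery.

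**The concern.** A per-protocol result is normally read as the effect among participants who followed the assigned regimen. Here the regimen is twice-daily toothbrushing and daily interdental brushing until delivery. The stated definition does not refer to it. It refers only to whether outcome data are complete, which is a condition on data capture observed after randomisation.

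Two things are at stake. First, readers of the trial report would take the result as evidence about use of the brushes, which this set cannot give. Second, the wording does not say which outcomes make up the complete set. On a wide reading, a woman whose PE status is known could be excluded because a late oral or microbiological measure is missing.

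**Working it through.** **Step 1: who is in the set.** Classify intervention-arm women by brush use and by completeness of outcomes.

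| Uses the brushes | Outcomes complete | Set as written | Set based on adherence |
|---|---|---|---|
| Yes | Yes | In | In |
| Yes | No | Out | In |
| No | Yes | In | Out |
| No | No | Out | Out |

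The set as written follows the second column only. In the two middle rows it does the opposite of what its name says.

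**Step 2: the stated method.** The analysis is to use the intention-to-treat methodology, which rests on multiple imputation. A set restricted to women with complete outcomes has no outcome left to impute. The sentence therefore describes a complete-case counterpart to the imputed analysis.

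**Step 3: what the complete set may contain.**

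- *Narrow reading, PE status only (or PE with the delivery outcomes).* These come from medical records after delivery (section 2.6.4). Early delivery does not by itself remove a woman.
- *Wide reading, all primary and secondary outcomes.* Interdental sampling is at 6 and 8 months (section 2.6.3), and Table 1 runs the oral examination monthly to 9 months. A woman who delivers before these visits cannot supply the measures and would be dropped, although her PE status is collected after delivery.

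The text does not choose between the two.

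**Step 4: illustration under the wide reading.** The protocol gives no figure for outcome-related missingness, so this shows how the result could move and does not estimate a bias. Inputs from section 2.7: PE risk 20% in control and 12% in intervention (8 points), and 10% dropout. The quantities f and r below are assumptions.

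*(a) A fraction f of PE cases is lost in each arm, and no non-cases.* Observed risk = p(1 − f)/(1 − pf).

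- f = 0.25: 0.15/0.95 = 15.8% and 0.09/0.97 = 9.3%; difference 6.5 points; risk ratio 0.59.
- f = 0.5: 0.10/0.90 = 11.1% and 0.06/0.94 = 6.4%; difference 4.7 points; risk ratio 0.57.
- Odds ratio with full data: (0.12/0.88)/(0.20/0.80) = 0.545. At f = 0.5: (0.06/0.88)/(0.10/0.80) = 0.545, unchanged.
- The risk ratio with full data is 0.12/0.20 = 0.60, so it hardly moves.

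*(b) 10% of each arm is missing, with PE risk r times that of completers.* Since p = 0.9 × observed + 0.1 × r × observed, observed risk = p/(0.9 + 0.1r).

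- r = 1 in both arms: 20% and 12%; 8.0 points, no bias.
- r = 2 in both arms: 0.20/1.1 = 18.2% and 0.12/1.1 = 10.9%; 7.3 points.
- r = 2 in control and 0.5 in intervention: 0.20/1.1 − 0.12/0.95 = 5.6 points.
- r = 0.5 in control and 2 in intervention: 0.20/0.95 − 0.12/1.1 = 10.1 points.
- No true effect (20% in both arms), r = 1 in control and 2 in intervention: 20.0% − 18.2% = 1.8 points, spurious.

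Missingness related to PE shifts the absolute risks and their difference even when it is equal in the two arms. In these examples a false difference under no effect arises only when it is unequal. If missingness is unrelated to PE, nothing moves.

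**The case against.** Four counter-arguments deserve an answer.

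**A reader might infer that the set selects on the outcome and removes PE cases preferentially.** The documents do not support that as a statement of fact. The condition is completeness of data, not the outcome value, and PE is collected from delivery records. Preferential loss needs the wide reading of an ambiguous phrase. The fractions in step 4(a) have no source in the protocol, and under equal loss the odds ratio does not change. A fall from 8 to 4.7 points should therefore not be presented as the expected distortion.

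**A reader might infer that the plan ignores adherence.** It does not. The sentence just before plans to exclude deviating clinics and individuals. This stands, and it makes the remedy easier: the plan has both a deviation-based and a complete-case analysis, with the label on the wrong one. It does not rescue the definition, because the two are set out as separate analyses.

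**A reader might object to excluding whole clinics.** Dropping any randomised unit or participant after allocation departs from the randomised comparison, and so would an adherence filter on women. In a trial randomised by clinic, a clinic-level explanatory analysis is a reasonable choice. This is a matter of preference and not an error.

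**Detailed criteria may sit in an analysis plan that is not shown.** That is fair for the deviation criteria, and their absence from the article is not faulted. The per-protocol definition is different: the article states it. An unseen plan could only repeat it or contradict it.

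**Conclusion.** The point holds as a wrong definition. The set called per-protocol is a complete-case set with no adherence condition, and a result reported under that name would misstate what is estimated. This follows from the text alone and needs no assumption about the data.

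Whether the set is also biased, and by how much, cannot be determined from the protocol. It depends on whether the complete set reaches beyond PE status to the late oral and microbiota measures, and on whether missingness is related to PE and is equal across arms. The range of 5.6 to 10.1 points around the planned 8 holds only for the assumed values of r between 0.5 and 2.

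The consequence is limited. The final analysis is by intention to treat on imputed data from all women, and the per-protocol analysis is additional to it. The correction is still worth making, because the error is clear and cheap to remove.

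**What to change.** 1. Rename the present analysis a complete-case sensitivity analysis to the imputed intention-to-treat analysis, and require only the primary outcome, PE status. This also removes the ambiguity about late oral and microbiota measures.
2. Attach the per-protocol label to the already planned analysis that excludes protocol deviators. Fix the deviation criteria before unblinding, using the compliance data already collected in the intervention arm. Because compliance answers exist in one arm only, seeing them would reveal the allocation, so the criteria are best written before those data are opened.
3. Keep this analysis supportive and adjust it for baseline covariates.
4. State that adherence is recorded in one arm only, so the set is selected asymmetrically and its comparison is no longer protected by randomisation. A matching criterion in the control arm would need a new question there.

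The cost is a change of wording and a written list of deviation criteria, with no new data collection unless a control-arm criterion is wanted. The downside is a smaller per-protocol set and a limitation that must be reported with it.

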## 2. Material and Methods

### 2.1. Trial Design

This study protocol is reported according to the Standard Protocol Items: Recommendations for Interventional Trials (SPIRIT) guidelines [29]. This trial is designed as a two-arm, parallel, cluster randomized controlled trial with antenatal obstetric clinic as the unit of randomization and an allocation ratio of 1:1 (Figure 1). 

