### 2.8. Recruitment

OP-PE trial will recruit 55 pregnant woman from each of the 16 clinical sites for a total of 880 subjects.

To identify participants, at the first visit for a pregnancy diagnosis, the physician will suggest that women who are less than 12 weeks pregnant, between the ages of 18 and 35, and who have never been pregnant before, participate in the study. If she responds positively, she will receive a trial information sheet and a consent form, and an inclusion visit will be scheduled by a qualified dental personnel. The total number of patients screened and recruited will be tracked. Patient volunteers will receive financial compensation.

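### With 16 clinics, the primary cluster-adjusted test needs a stated small-sample reference; the usual chi-square or normal one gives about 6% one-sided error at nominal 5%

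*Protocol article*

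**What the plan says.** - **Design.** Section 2.1 describes a parallel cluster trial with "antenatal obstetric clinic as the unit of randomization and an allocation ratio of 1:1". Section 2.8 recruits "55 pregnant woman from each of the 16 clinical sites". Section 2.9.1 stratifies the clinic allocation by study site and clinic characteristics and does not give the number of strata.
- **Primary analysis.** Section 2.10.3 names as the main technique a Mantel–Haenszel "test adapted to the cluster randomization design". It then adds Kaplan–Meier estimation with "comparison of the different groups by the Log Rank test" at p < 0.05, and a Cox model in an exploratory role. Continuous outcomes go to mixed models with clinic as a random effect.
- **Error rate.** Testing is one-sided, both in Section 2.10.3 and in Section 2.7, where "in a unilateral proportion test, we initially calculated 440 subjects per group". Alpha is 5%.
- **Clustering.** Section 2.10.3 says that all analyses will allow for correlation within clinics. It gives no variance estimator, reference distribution or degrees of freedom, and it neither applies nor excludes a small-sample correction.

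**The concern.** Adapting a Mantel–Haenszel or log-rank test to clusters changes the variance in the denominator. It does not change the curve from which the p-value is read, and in their usual form both statistics are read from a chi-square or normal curve. That curve treats the variance as known. Here the variance is estimated from 16 clinics, and its own uncertainty makes the statistic heavier-tailed than normal. The promise to account for within-clinic correlation deals with the first issue and leaves the second open.

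At stake are the p-value that decides the trial and the width of the interval around the effect. A one-sided 5% threshold is already lenient. If the reference distribution is chosen after the data are seen, that choice could settle a borderline result.

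**Working it through.** **Inputs.** 16 clinics of 55 women (Section 2.8); 1:1 allocation by clinic (Section 2.1); PE 20% versus 12%, ICC 0.03, one-sided alpha 5%, power 80% (Section 2.7, where the beta of 80% is read as power).

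**The plan's own figure.** The article states no achieved error rate, only the nominal 5%. Its one computed figure is 440 per group. Two proportions under individual randomization, one-sided, pooled variance under the null:

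n = [1.645 × √(2 × 0.16 × 0.84) + 0.842 × √(0.20 × 0.80 + 0.12 × 0.88)]² / 0.08² ≈ 259 per arm.

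Design effect = 1 + (55 − 1) × 0.03 = 2.62, and 259 × 2.62 ≈ 679 per arm. So 440 is not reproduced; it would fit a cluster size of (440/259 − 1)/0.03 + 1 ≈ 24. That is a separate matter. It explains why the power below starts near 65% and not 80%.

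**Step 1, degrees of freedom.** 16/2 = 8 clinics per arm; 16 − 2 = 14.

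**Step 2, analytic size.** The chance that a t statistic passes the normal critical value (1.645 one-sided, 1.960 two-sided):

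| df | one-sided | two-sided |
|---|---|---|
| 14 | 6.1% | 7.0% |
| 13 | 6.2% | 7.2% |
| 12 | 6.3% | 7.4% |
| 10 | 6.6% | 7.8% |
| 8 | 6.9% | 8.6% |

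The rows below 14 show what happens if strata are carried into the analysis; how many there are is an assumption. By the first row, a nominal 95% interval built with 1.960 covers about 100 − 7.0 = 93.0%. The t multiplier on 14 df is 2.145, so a correct interval is 2.145/1.960 ≈ 1.09 times as wide.

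**Step 3, simulated size.** Beta-binomial clinics with no treatment effect, 8 + 8 clinics of 55, ICC 0.03, no strata, nominal one-sided 5%:
- ICC-adjusted chi-square (the single-stratum form of the cluster-adapted Mantel–Haenszel test) with a normal reference: 5.9–6.1% over PE rates of 12%, 16% and 20%.
- t on 14 df: 4.8–5.1%.
- With ICC between 0.01 and 0.05, the normal-reference test stays at 5.6–6.1%.
- With 2 to 4 assumed strata in the analysis: 6.2–6.8%.

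With 200,000 trials per setting, the Monte Carlo standard error is √(0.06 × 0.94/200,000) ≈ 0.05 points, so the excess is not noise.

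**Step 4, the log-rank comparison.** 20,000 simulated trials, PE 20%, ICC 0.03. A cluster-robust log-rank score test with a normal reference rejects in 5.7% one-sided (5.3% two-sided).

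**Step 5, power at 20% versus 12%.** Effective size per arm = 440/2.62 ≈ 168.
- Standard error under the alternative = √(0.2656/168) ≈ 0.0398; under the null = √(0.2688/168) ≈ 0.0400.
- Normal reference: Φ[(0.08 − 1.645 × 0.0400)/0.0398] ≈ 64%.
- t on 14 df, noncentrality 0.08/0.0398 ≈ 2.01: about 61%.
- Simulation agrees: 65.2% against 61.1%.

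**The case against.** The strongest reply is that the article is silent and has not chosen wrongly. A journal article condenses a fuller protocol, the analysis plan is not shown, and the reference distribution is often settled there. A corrected variance or a permutation test would satisfy the wording of Section 2.10.3 and hold about 5%.

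Much of this stands. A reader might infer that the trial's error rate does exceed 5%; the article does not support that, because nothing in it excludes a correction. Four other inferences also go too far:
- **Error of 7–9%.** One-sided figures of 6.8–7.4% belong to a cluster-robust standard error with a normal reference, which the article never mentions. The 8–9% figures also require two-sided testing, and the plan is one-sided.
- **About 15% for the log-rank test.** That applies only if clustering is ignored, and Section 2.10.3 says it will not be.
- **The Cox model as a threat to the primary claim.** Its stated role is exploratory.
- **A free correction.** It is cheap, but it costs power.

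What does not stand is that there is nothing to raise. The article itself names the deciding tests, and both are large-sample tests in their ordinary form. An analyst who follows the text literally would take the large-sample reference, and the general statement on clustering would not prevent it.

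**Conclusion.** The point holds conditionally and is modest in size. If the cluster-adapted Mantel–Haenszel test is run with its usual chi-square or normal reference, one-sided error at nominal 5% is about 6%, and about 6–7% if strata are analysed. The log-rank comparison is affected less (5.7% in its cluster-robust score form). A t reference on 14 df restores about 5%.

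This rests on 8 equal clinics of 55 per arm (derived from the 1:1 ratio and 16 sites), beta-binomial variation between clinics, ICC of 0.01–0.05 (0.03 for the log-rank and stratified figures), and an assumed number of strata where strata enter. It is a cheap improvement to a named analysis and does not show that the trial's conclusion would be invalid.

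**What to change.** State in Section 2.10.3, before any unblinded analysis, one of the following for the primary cluster-adjusted test and its interval:
- a t reference with degrees of freedom equal to clinics minus 2 (14), reduced for any strata analysed; or
- a permutation test over the clinic allocation, re-randomizing as the trial did, within strata. Without strata there are 16!/(8! × 8!) = 12,870 allocations. With, for illustration, four strata of four clinics there are 6⁴ = 1,296, still enough for a 5% test.

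Apply the same principle to the log-rank comparison; permuting clinic labels does this directly. As secondary matters, use small-sample corrected standard errors and degrees of freedom in the exploratory Cox model and the mixed models. In simulation, an unadjusted Cox analysis with variance scaled by G/(G − 2), G being the number of clinics, and t on 14 df rejected in 5.0% one-sided.

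The cost is analysis code and about 4 points of power at 20% versus 12% (about 65% to 61% with 55 women in each of 8 clinics per arm). The stated power should be recalculated with the chosen reference.
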